## Methods/design

### Study design

A cohort design was chosen because an assessment of test combinations within a randomized controlled trial would require the evaluation of many diagnostic strategies for which the number of subjects needed would exponentially increase [13]. To determine the diagnostic value of emerging biomarkers for AD and related disorders both a clinical diagnosis and diagnosis based on emerging biomarkers (index tests) are compared with a reference diagnosis. Due to limited ability of biopsy (which is unethical) or autopsy (which requires follow up until death) a two-year follow up of the clinical course is used as a proxy to obtain information on the state of the disease at baseline; so-called delayed-type cross-sectional accuracy study design [12]. Four academic memory clinics (Leiden University Medical Centre, Maastricht University Medical Centre, Radboud University Nijmegen Medical Centre and VU University Medical Centre) specialized in the diagnosis and treatment of memory disorders participate in the study. Two memory clinics are settled within a department of geriatrics, one within neurology and one within psychiatry. The study is performed within the framework of CTMM, the Center for Translational Molecular Medicine (http://www.ctmm.nl), a Dutch public-private partnership; project LeARN (grant 02 N-101).

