### Sample size and missing data

A telephone interview is performed for patients who refuse follow-up assessments to determine the reason for refusal, possible cognitive decline and interference with daily activities, and to assess the CDR. Incomplete data will be imputed by means of a regression model. Complete missing data or data missing covariates will be imputed using Rubin’s multiple imputation (MI) procedure.

Sample size is based on an 80% accuracy of current clinical practice to determine correct aetiology [4] and 70% in non-demented patients [49]. Applying a type I error (α = 5%), type II error (β = 80%), drop-out rate of 10% and minimum clinically relevant difference of 10% accuracy increase requires 219 patients to be included in the study.

Contrary to clinical studies, economic evaluations are not based on testing hypotheses. Their goal is to assess decision uncertainty. Therefore, economic evaluations are restricted to the estimation of the uncertainty surrounding cost-effectiveness (expressed in a statistical confidence interval). Within this Bayesian framework, classical inference (and therewith a power analysis) is irrelevant [50].

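### The sample-size paragraph labels 80% as the type II error (β); this literally means 20% power and does not fit the 219 patients in the same sentence

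*Protocol article*

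**What the plan says.** All the inputs stand in the second paragraph of *Sample size and missing data* in the protocol article.

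- Reference accuracy: "Sample size is based on an 80% accuracy of current clinical practice to determine correct aetiology", with a second value of "70% in non-demented patients".
- Type I error: "Applying a type I error (α = 5" per cent).
- Type II error: "type II error (β = 80" per cent).
- Drop-out: "drop-out rate of 10" per cent.
- Effect: "minimum clinically relevant difference of 10% accuracy increase".
- Result: the calculation "requires 219 patients to be included in the study".

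No other section gives a power for the accuracy comparison. The next paragraph of the same section sets power analysis aside for the economic evaluation only, and the Discussion mentions power only as a drawback of a randomised trial. *Study design* describes one cohort in which "both a clinical diagnosis and diagnosis based on emerging biomarkers (index tests) are compared with a reference diagnosis".

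**The concern.** The type II error is the probability of missing a difference that is really there, and power is one minus that probability. Both the words and the Greek letter in the article name the type II error, so the printed 80% means a power of 1 − 0.80 = 20%. That would be a very unusual design target. It also sits in the same sentence as a sample size that looks far too large for it.

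This sentence is the article's only justification of the size of the diagnostic accuracy study (research goal 1). A reader who enters the inputs as printed will not obtain 219 by the ordinary calculation and has to guess which input is wrong.

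**Working it through.** **Inputs from the article** (*Sample size and missing data*): α = 0.05; β = 0.80 as printed; accuracy 0.80 for current practice; gain 0.10; drop-out 0.10; result 219.

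**Assumptions the article does not state:** a two-sided test; an absolute gain (0.80 to 0.90); the normal-approximation formula for two proportions, with the per-group n taken as the size of the single cohort; drop-out handled as n/0.9, rounding up at each step.

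**Step 1. Reproduce 219 with β = 20%, unpooled variance.**

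n = (z₁₋α/₂ + z₁₋β)² × [p₁(1 − p₁) + p₂(1 − p₂)] / d²

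- z values: 1.960 and 0.842; the squared sum is 7.849.
- Variance term: 0.80 × 0.20 + 0.90 × 0.10 = 0.25; divided by 0.10² this is 25.
- n = 7.849 × 25 = 196.2, rounded up to 197.
- 197/0.9 = 218.9, rounded up to **219**, the stated figure.

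**Step 2. Same formula with β = 80% as printed.** The second z value becomes −0.842.

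- (1.960 − 0.842)² = 1.251.
- n = 1.251 × 25 = 31.3, rounded up to 32.
- 32/0.9 = 35.6, rounded up to **36**, about one sixth of 219.

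**Step 3. Pooled variance.**

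n = [z₁₋α/₂ √(2p̄(1 − p̄)) + z₁₋β √(p₁(1 − p₁) + p₂(1 − p₂))]² / d², with p̄ = 0.85

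- β = 20%: (1.960 × 0.505 + 0.842 × 0.5)²/0.01 = 199.0, so 199; 199/0.9 = 221.1, so 222. (Inflating by 1.1 instead gives 218.9, so 219.)
- β = 80%: (1.960 × 0.505 − 0.842 × 0.5)²/0.01 = 32.4, so 33; 33/0.9 = 36.7, so 37.

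| Formula (0.80 vs 0.90, two-sided 5%) | β = 80% as printed: n (with drop-out) | β = 20%: n (with drop-out) |
|---|---|---|
| Unpooled | 32 (36) | 197 (219) |
| Pooled | 33 (37) | 199 (222) |

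**Step 4. Could another method rescue β = 80%?** One-sample, McNemar, arcsine and continuity-corrected formulas were tried, one- and two-sided, with starting accuracies of 0.70, 0.75 and 0.80. With an absolute gain of 10 points, the largest result at 20% power is 147: 0.70 versus 0.80 with continuity correction needs 66 per group, two groups make 132, and 132/0.9 = 146.7.

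One route does come close. If the 10% is read as relative (0.70 to 0.77) and two independent groups are added together, the unpooled formula gives 99 per group, 198 in total, and 198/0.9 = 220; the pooled one gives 100, 200 and 223.

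**Step 5. Is Step 1 the only route to 219?** No. At 80% power, two-sided, a one-sample formula with the variance at the target value gives 7.849 × 0.09/0.01 = 70.6 (71) for 80% to 90% and 7.849 × 0.16/0.01 = 125.6 (126) for 70% to 80%; together these make 197, and again 219. The formula actually used cannot be identified from the article. Both of these exact matches use β = 20%.

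**The case against.** **It is an obvious slip with no effect on the study.** Most of this stands. The 219 fits a power of 80%, and *Subjects* reports that 241 patients were included, more than 219. Correcting the label changes no sample size and no analysis. What does not follow is that the sentence can be left alone: it is a wrong statement of a key design parameter, not a detail left to a fuller document, and nothing else in the article corrects it.

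**The match to 219 is an inference.** This stands too. Test, formula and sidedness are not given, and a condensed article may leave them to the full protocol, so their absence is not a criticism here. The per-group number from a formula for two independent groups is used for a single cohort. A reader might infer that 219 can arise only with β = 20%. That is too strong, because the relative-increase route in Step 4 gives 220 to 223 at 20% power. However, it needs two separate groups, whereas *Study design* describes one cohort with the diagnoses compared in the same patients, so the near match is best taken as coincidence.

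**A reader might infer that the study accepts missing a relevant gain four times in five.** That is the literal meaning of the printed β, but the article's own 219 speaks against it: a study sized at 20% power under the ordinary reading would have asked for about 36 patients.

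**Conclusion.** The article prints 80% as the type II error, and this cannot be reconciled with the 219 patients under any ordinary reading of its own inputs. Like for like, the printed β leads to 36 (unpooled) or 37 (pooled) patients including drop-out, and β = 20% leads to 219 or 222. The 80% is almost certainly the power, mislabelled as β.

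The figures rest on a two-sided 5% level, an absolute 10-point gain from 80%, the per-group n used as the cohort size, and division by 0.9. The conclusion about the label is firmer than the choice of formula: no formula tried with an absolute 10-point gain exceeds 147 at 20% power.

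The finding goes no further. It does not show that the study was planned at 20% power or is underpowered, and it gives no reason to change 219. Whether an unpaired formula suits a within-patient comparison is a separate question that this error does not settle.

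**What to change.** Check the original sample-size calculation. If it used 80% power, as the arithmetic indicates, restate the input in *Sample size and missing data* as type II error β = 20% (power 80%). If the check shows another intended value, state that value together with the sample size that follows from it.

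The cost is a look at the original calculation and one corrected figure. This error alone calls for no change to the sample size, data collection or analysis.

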### Ethical considerations

According to the medical ethics committee “MedischEthischeCommissieazM/UM” the research protocol complies with the Declaration of Helsinki (October 2008, http://www.wma.net, ref.nr.: MEC 09-3-038) and with the Medical Research Involving Human Subjects Act and codes on ‘good use’ of clinical data and biological samples as developed by the Dutch Federation of Medical Scientific Societies.

## Discussion

This research protocol describes the methods used to assess the clinical and economic value of new diagnostic approaches for the diagnosis of AD. A delayed-type cross-sectional accuracy study design is chosen because a randomized clinical trial comes with ethical issues, long follow-up time and limited power. Two hundred forty one consecutive patients suspected of having a primary neurodegenerative disease are followed up for two years and a reference diagnosis is determined by an independent consensus expert panel. Eligibility criteria are chosen to maximally reflect a patient cohort within clinical practice.

Several other multi-centre trials study the relative value of new biomarkers for early evaluation of AD and related disorders. The Alzheimer’s Disease Neuroimaging Initiative (ADNI) in North America is aimed to identify neuroimaging measures and biomarkers associated with cognitive and functional changes in healthy elderly subjects and in subjects who have MCI and AD [51]. Furthermore, the ‘Development of Screening Guidelines and Clinical Criteria for Predementia AD’ (DESCRIPA) study is aimed to develop screening guidelines for predementia AD in the general population [52]. Both include markers in PET, MR imaging and CSF. The uniqueness of this study is the assessment of resource utilization and quality of life to enable an economic evaluation. Furthermore, the decision analytic model enables the evaluation of the optimal diagnostic strategy and the evaluation of diagnostic techniques to be developed during the study in sub-cohorts of the study population. At last, without a disease modifying treatment, the added value of biomarkers is uncertain. Therefore, the availability of such treatment is explored in the sensitivity analysis.

The study has some limitations. It focuses on applying new tests for diagnostic or prognostic goals. Screening and treatment monitoring are outside the scope of this study. A follow-up period of two years was taken as a compromise to maximise the time for the disease to express symptoms of progression (to prevent false negative reference diagnoses) and to minimize the time to prevent the start of a new disease episode after the baseline assessment (to prevent false positive reference diagnosis). It may take up to 10 years before all symptoms of dementia come to expression in subjects with AD pathology [53].

The study results are generalizable to a population of patients who are referred to a memory clinic of a university medical centre due to their memory problems.
